### Identification of “High-Risk” Patients

High-risk patients will be identified using 2 methods:

A risk prediction model (phase 1: part B) to identify patients who are at high-risk of medication-related readmission.Identification by the cardiology treating teams and the cardiology ward pharmacist, who refer patients to the TOC service.

### RECARD Intervention: Pharmacist-Led TOC Service

Following patient consent, the TOC team will deliver assessments, activities, and medication reviews during the patient’s inpatient stay and for the 30 days postdischarge. The timeline for participant enrollment and assessments is shown in Table 1, created per the SPIRIT guidelines [23].

**Table 1. T1:** Participant timeline for enrollment and assessments during the trial period.

Time point	Enrollment	Intervention			Closeout
	During hospital admission	Discharge from hospital	Day 3 postdischarge	Day 14 postdischarge	Day 30 postdischarge
Enrollment					
Eligibility screen	✓				
Informed consent	✓				
Assessments					
Adherence assessment		✓		✓	
Pharmacist activities			✓	✓	
Nurse practitioner consult				✓	
Patient experience survey					✓

The RECARD activities will be described in an intervention bundle that is provided to support the decision-making capabilities of the TOC clinicians. Furthermore, this bundle is intended to empower TOC clinicians to make critical judgments when tailoring the TOC service to individual patients (eg, not repeating tasks that have been performed by ward pharmacists or not offering services that would be foreseeably ineffective).

The bundle will be developed based on previous work by the research team, including findings from a scoping review [1], local studies exploring TOC at the participating sites [33], and qualitative studies with clinicians and patients as part of the larger RECARD program (HREC/2023/MNHB/104151 [25]).

The work conducted in phase 1 seeks to inform the development of this bundle (see phase 1) [1]. The TOC service will be tailored to patients based on an assessment and identification of their individual needs and delivered during the hospital admission and across care transitions (Figure 3).

**Figure 3. F3:**
[figure not shown]
RECARD TOC study interventions across hospital transitions of care. CP: community pharmacy; HMR: home medicine review; GP: general practitioner; NRT: nicotine replacement therapy; RECARD: Reduce Hospital Readmissions for High-Risk Cardiology Patients; TOC: transition of care.

### Description of the TOC Service Model and Activities in the Bundle of Care

TOC services have many steps at which communication between patients and clinicians can occur (Figure 3). Table 1 highlights the potential touchpoints in the patient journey where various activities are provided to intervention participants as part of the TOC service. Typical activities delivered throughout a patient’s inpatient stay and in the postdischarge setting are described below [34]. The clinical skill set of NPs allows them to modify medication dosing, provide pathology requests, undertake patient observations, and interpret patient symptoms. In collaboration with the TOC pharmacist, the NP will run a 1-day-per-week clinic for patients who have specific comorbidities, pathology, physiology, or electrolytes requiring follow-up and patients with newly prescribed, withheld, or dose changes to β-blocker and angiotensin-converting enzyme inhibitor/angiotensin receptor blocker medications.

### Medication Education

Medication education is defined as the provision of tailored counseling (ie, having a conversation with the patient and/or their caregiver about their medications) delivered by a health care professional [35]. This includes informing the patient of any changes to their medication regimen (ie, ongoing medications, new medications, changed medications, or discontinued medications). The provision of medication education can occur at any time point across the continuum of a patient’s health care [36]. Additionally, this TOC service will ensure that all written medication lists provided to the patient are communicated to both the patient’s GP and community pharmacy after their education with the RECARD pharmacist.

### Disease-Specific Education

The TOC pharmacist, in liaison with a NP, will offer to provide lifestyle and, where required, disease-specific education, which may include counseling on modifiable risk factors such as diet, exercise, and smoking. This may also include the initiation or continuation of smoking cessation programs or nicotine replacement therapy, where appropriate. Disease-specific activities provided by the team may include further education on aspects such as symptom monitoring that are relevant to the patient’s cardiovascular condition (eg, salt intake or weight monitoring).

### Adherence Assessment and Provision of Adherence Aids

The TOC pharmacist will conduct a medication adherence assessment using 2 validated self-report tools, including the Medication Adherence Report Scale-5 [37,38]. An adherence assessment will be conducted as an inpatient activity (baseline) and as a postdischarge activity (follow-up). The adherence assessment will be used to tailor the information provided and identify interventions implemented for each individual identified as being at high risk of medication-related problems. If patients are assessed as nonadherent to their medications, the TOC team can implement an appropriate strategy to support medication adherence.

### Hospital Discharge Planning and Completion

The team engages in a collaborative decision-making process to determine a discharge plan and identify when the patient is ready for discharge. If the patient has consented to the TOC service, the ward pharmacist will provide a handover of all key issues and care provided for the patient during hospitalization to the TOC pharmacist. The TOC pharmacist must review prescriptions for clinical, ethical, legal, and Pharmaceutical Benefits Scheme requirements in accordance with relevant guidelines and standards. The TOC pharmacist will reconcile the medications prescribed at discharge. To complete the discharge process, the TOC pharmacist will also complete a discharge medication record (DMR), which is a list that encompasses a written description of instructions for discharge medications, a record of medication changes, and actions or updates for the patient and the primary care provider. Completion of the patient’s discharge also involves reviewing the discharge plan and undertaking any required actions, organizing prescriptions, and ensuring medication supply, if needed.

### Handover to Primary Care Provider

The TOC team will provide the DMR and other relevant discharge information to the primary care provider (GP and/or community pharmacist) using written and, potentially, verbal communication over the phone.

### Postdischarge Follow-Up Consults and Medication Optimization

The TOC team will organize a follow-up consultation with the patient through the platform of their preference (ie, in person, by video, by phone call, or through a home visit) and will confirm a date and time for this consultation within 14 days postdischarge (maximum 30 d). The follow-up consultation will encompass activities described above, such as medication review and optimization, medication education, and lifestyle education tailored to the patient. An updated medication record (same format as the DMR) will be provided to the patient if any changes have been made to their medication regimen since discharge. The TOC team will answer any questions or concerns, resolve any medication issues that arise during the follow-up consultation, and consolidate the medication education provided on discharge, if relevant. The TOC team will refer any issues to the treating team or primary care provider where appropriate. Home visits provide a unique opportunity to review a patient’s medicine stocks and storage practices. While the RECARD TOC team hopes to undertake some home visits where appropriate, this will not be possible for all patients requiring a home visit, especially those who live outside the hospital’s local area. For these patients, the TOC pharmacist will arrange a hospital-initiated Home Medicine Review referral. The Home Medicines Review pharmacist and TOC pharmacist will liaise to ensure the appropriate management of medication-related issues.

### Culturally Safe Care

The TOC team will aim to provide culturally safe care to all patients, guided by information collected in the yarning circles conducted in phase 1. For patients identifying as Aboriginal and/or Torres Strait Islander, this care will be guided and supported by an Indigenous health worker. The Indigenous health worker will yarn with Aboriginal and Torres Strait Islander patients as needed to help identify the challenges they are experiencing and engage them with the pharmacist, NP, and rehabilitation programs.

### Usual Care

Usual care across the hospital sites includes nurse and pharmacist involvement during admission and at discharge (as resources permit), according to standard operating procedures. All patients who are not identified as being at high risk of readmission during the intervention period, along with all patients in the prestudy period (usual care control group), will receive usual care and will not be provided the interdisciplinary pharmacist-led TOC service. Usual care typically does not include dedicated pharmacy support as part of postdischarge follow-up.

### Outcome Measures

#### Primary Outcome: Medication-Related Hospital Readmissions and Causality Analysis

All patients who are readmitted to the hospital within 30 days following discharge from the PAH, RBWH, or TUH will be retrospectively reviewed to identify whether their readmission was medication-related.

For the primary outcome of 30-day medication-related hospital readmissions, cases will be confirmed and validated using a bimodal approach. The first will include the use of *International Statistical Classification of Diseases and Related Health Problems, Tenth Revision, Australian Modification* (*ICD-10-AM*) “Y” codes to determine “drugs, medicaments and biological substances causing adverse effects in therapeutic use.” The second approach will involve the review of the patient discharge summary, progress notes, and laboratory markers by 2 senior pharmacists to confirm 30-day medication-related readmission.

Finally, an expert panel comprising a senior pharmacist, specialist nurse, cardiologist, and researcher will independently review readmissions to reach a final consensus. The expert panel will confirm medication-related hospital readmissions by assessing causality using tools such as the Naranjo algorithm or the World Health Organization Uppsala Monitoring Centre criteria.

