###### Outcome

Medication-related hospital readmissions within 30 days of hospital discharge will be identified through a comprehensive retrospective review of patient clinical records by 2 senior pharmacists. Causality, preventability, and severity of potential medication-related hospital readmissions will be reviewed and rated by a panel of clinicians, including a cardiologist, nurse practitioner (NP), and pharmacist.

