### Sample Size

It is expected that, under conditions of usual care, the rate of medication-related hospital readmissions within 30 days among patients discharged following an AMI is 7% [40]. Interventions have reduced this rate from 7% to 4.9% (an absolute risk reduction of 2.1%) [41]. As mentioned previously, only a subset of the population (those identified as being at highest-risk based on model scoring and/or clinician referral) will be targeted to receive the intervention. Guided by previous studies and resources, we expect to prioritize the top 25% of patients at high-risk of medication-related readmission [42]. An additional 10% of patients are expected to be referred by the treating team. However, the final proportion of patients who will be triaged for intervention will be guided by a local audit following the development of the risk model. Because the high-risk patients will likely have a higher rate of potential readmission (ie, >7%), we expect that an intervention applied to only this group will still produce an absolute risk reduction of at least 2.1% averaged across the entire intervention sample, even though we expect the risk in the low-risk group to remain unchanged. Therefore, the sample size calculation is based on the overall sample required, not just the high-risk group.

Assuming a baseline risk of readmission of 7% and a significance level of .05, a sample size of 1990 participants is required in both the prestudy and intervention periods (ie, a total of 3980 patients across both prestudy and intervention periods) to detect an absolute risk difference of 2.1% with a power of 0.80. We assume a minimal dropout and refusal rate of 10%; taking this into account, we aim to recruit 2211 participants into each 12-month period (a total of 4422 participants across both the prestudy and intervention periods). We expect 35% of patients (~775 patients) to be flagged as high risk, consent to the study, and be given the TOC intervention. The remainder of the patients enrolled in the study will be given usual care as described earlier. Delivering the TOC service to 775 participants across the study sites over 12 months is both logistically feasible and achievable.

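### The primary outcome is a causality judgement compared between calendar periods, with no stated masking and no fixed causality tool, so a shift in rating between periods cannot be separated from the service effect

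*Protocol article*

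**What the plan says.** Protocol article, *Primary Outcome: Medication-Related Hospital Readmissions and Causality Analysis*: every 30-day readmission is reviewed retrospectively. Candidates are identified by ICD-10-AM Y codes and by two senior pharmacists who read discharge summaries, progress notes and laboratory results. The last step is that "an expert panel comprising a senior pharmacist, specialist nurse, cardiologist, and researcher will independently review readmissions to reach a final consensus". The panel "will confirm medication-related hospital readmissions by assessing causality using tools such as" the Naranjo algorithm or the WHO-UMC criteria. No single tool and no cut-off are fixed, and nothing is said about masking, redaction or the order of review.

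*Statistical Analysis*: the primary comparison is the prestudy cohort against the poststudy cohort, by logistic regression on study period plus patient confounders such as age and sex.

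*Phase 1 Part B* (Methods and Outcome): the risk model uses 1000 patients from PAH or TUH, July 2023 to June 2024. Their 30-day readmissions are screened by two senior pharmacists, and causality is "reviewed and rated by a panel of clinicians, including a cardiologist, nurse practitioner (NP), and pharmacist". *Precohort* covers the same 12 months, and PAH and TUH are two of the three trial sites. *Results* reports that the risk tool has been developed.

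*Limitations* names changes over time in patients and in clinical practice. It does not name changes in how the outcome is assessed.

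**The concern.** Whether a readmission is medication-related depends on the assessor, the tool and the information in the file. In a design with concurrent controls, a drift in strictness would affect both groups. Here exposure is calendar period, so a drift between the two reviews lines up exactly with the intervention. Adjusting for age, sex or comorbidity does not touch it, because it is a property of the measurement and not of the patient.

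The direction is not known in advance. Assessors who know that a pharmacist-led service was running may be less ready to call a post-period event medication-related. Against that, the service generates extra medication records (a discharge medication record and, where the regimen has changed, an updated record at follow-up), while usual care typically has no dedicated pharmacy follow-up. Fuller files could lead to more events being recognised. The first error would manufacture a benefit and the second would hide one.

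The Phase 1B overlap adds a specific route. If ratings made for model development were carried into the precohort, part of the pre rate would come from a separate rating exercise.

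**Working it through.** **Inputs from *Sample Size*.** "Assuming a baseline risk of readmission of 7% and a significance level of .05, a sample size of 1990 participants is required" per period, "to detect an absolute risk difference of 2.1% with a power of 0.80", and "we aim to recruit 2211 participants into each 12-month period". The post rate under the alternative is 4.9%.

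**Reproducing the plan's figure.** Two-sided test, pooled variance, no continuity correction:
n = [1.96·√(2·0.0595·0.9405) + 0.8416·√(0.07·0.93 + 0.049·0.951)]² / 0.021² = 1990.8, against the stated 1990. Dividing by 0.9: 1990/0.9 = 2211.1, against the stated 2211. Both reproduce. Power at 2211 per period is 84%.

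**Effect of a rating shift when the service does nothing.** The true rate is 7% in both periods. In the post period assessors confirm a fraction x fewer of the same events, so p₂ = 0.07(1 − x). The probability of a significant apparent benefit is Φ((d − 1.96·SE₀)/SE₁), where d = 0.07 − p₂, SE₀ is the pooled and SE₁ the unpooled standard error. Two-sided rejection adds the opposite tail. The documents give no value for x, so a range is shown.

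For x = 10% and n = 2211: d = 0.007, SE₀ = 0.00749, SE₁ = 0.00749; (0.007 − 0.01469)/0.00749 = −1.026; Φ = 0.152; the opposite tail adds 0.002, giving 15.4%.

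| Assumed drop in confirmation, all post events | Apparent reduction (points) | Share of the 2.1-point target | Two-sided rejection, 2211 per period | Same, 1990 per period |
|---|---|---|---|---|
| 0% | 0 | 0 | 5.0% | 5.0% |
| 5% | 0.35 | 1/6 | 7.5% | 7.2% |
| 10% | 0.70 | 1/3 | 15.4% | 14.4% |
| 20% | 1.40 | 2/3 | 48.2% | 44.4% |
| 30% | 2.10 | all | 84.0% | 80.0% |

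**Shift confined to service patients.** Assume they carry half of the post events: p₂ = 0.07(1 − 0.5x). At 2211 per period, x = 10/20/30% gives 7.5/15.4/29.4% rejection.

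**Shift confined to Phase 1B ratings, if these were reused.** Maximum share of the precohort: 1000/2211 = 45% (1000/1990 = 50%). At 7% that is about 70 of 155 expected pre events. If the Phase 1B panel confirmed 10/20/30% more, p₁ = 0.07(1 + 0.452x), the apparent reduction is 0.32/0.63/0.95 points, and rejection at 2211 per period is 6.9/12.8/22.5%.

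**Opposite direction.** If the service truly achieves 4.9% but 10% more events are confirmed post, the observed post rate is 0.049 × 1.1 = 5.39% and the apparent reduction 1.61 points. With SE₀ = SE₁ = 0.00725 to that precision, Φ((0.0161 − 0.01421)/0.00725) = Φ(0.26) ≈ 0.60. Power falls from 84% to about 60%.

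**The case against.** The strongest reply is that a journal article need not contain an adjudication manual. Masking and batch order may be set out in the full protocol, and silence does not show that they are absent. This is fair as far as masking goes. The open choice of tool is different: it is written into the outcome definition itself.

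A reader might infer that assessors see period and service notes. The article does not say so. It is a likely consequence of reading unredacted records, no more.

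A reader might also infer that a large part of the precohort has already been rated by a different panel and that those ratings will be used. The text does not support this. The Phase 1B membership list is not exhaustive and is compatible with shared members; completed ratings are only implied by the finished risk tool; and reuse is never stated. The Phase 2 text reads as one review of all 30-day readmissions, *Postcohort (Prospective Data Collection)* promises the same variables in both periods, and precohort data were still being collected. The 45% is also an upper bound: 1000 is a planned count from one or two hospitals, and trial exclusions may reduce it.

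Finally, not every drift biases the result. Only drift that differs between periods does. Y codes give one identification route that does not rest on the study's assessors, and independent multidisciplinary review tempers any allegiance to the pharmacist's role. The panel nevertheless has the final say, so the outcome remains a judgement.

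**Conclusion.** The concern holds in this form: the primary outcome is a chart-based causality judgement, no masking to period or service is stated, the tool is not fixed, and exposure is calendar period. A rating shift between periods is therefore confounded with the service. This part stands whether or not any Phase 1B rating is reused. How those ratings relate to the Phase 2 review is a separate gap that the article leaves open.

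The size depends on assumed drift. A 10% relative shift across all post events equals one third of the target effect and roughly triples two-sided rejection, from 5% to about 15%. It takes a 30% shift to imitate the whole planned effect. The two narrower mechanisms give about 7 to 7.5% at a 10% shift, so the 15% should not be quoted for them. The half share of events in service patients is also an assumption. The documents do not show that drift will occur or in which direction. They show that the stated procedure does not guard against it.

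**What to change.** State in the protocol that all pre and post 30-day readmissions are rated by the same panel, with one named causality tool and one fixed cut-off, in randomly mixed pre/post batches. Mask dates, period and service identifiers, but keep the medication-exposure facts needed to judge causality. Removing every service entry would delete drug information in treated patients only and could create the differential misclassification that masking is meant to prevent. Rate the overlapping Phase 1B readmissions again within these batches instead of carrying their labels over, and report agreement between the two sets of ratings. Add assessment drift to *Limitations*.

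The cost is redaction work by existing staff and re-rating of the readmitted subset of the development patients. No new assessor is needed. Masking will be imperfect where the notes reveal the service, but mixed order and a single tool still limit drift. There is time: recruitment runs to November 2026, analysis is planned for January to March 2027, and no preliminary analysis has been done. If this procedure is already in place, one sentence saying so settles the point.

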#### Secondary Outcomes

The secondary outcomes are summarized in Figure 4. The secondary outcomes have been chosen based on a hybrid effectiveness-implementation design to explore strategies to translate the intervention into practice and are mapped to the RE-AIM framework [20].

**Figure 4. F4:**
[figure not shown]
Mapping of secondary outcome measures in the RECARD trial using the RE-AIM (Reach, Effectiveness, Adoption, Implementation, and Maintenance) framework. AMI: acute myocardial infarction; CS: cardiothoracic surgery; RECARD: Reduce Hospital Readmissions for High-Risk Cardiology Patients; TOC: transition of care.

### Analysis Types of Harm

The severity and preventability of 30-day medication-related readmission will be assessed as a secondary outcome to assess the types of harm. Methods to assess preventability will include the use of the modified Schumock and Thornton criteria [21]. Methods to assess the severity of medication harm will follow the definitions described by Morimoto et al [22]. A multidisciplinary panel will also review preventability and severity of the medication-related hospital readmissions, as used for causality analysis.

